### 6.4 Missing Data

Missing data will be considered, and appropriate imputations will be discussed (and performed when appropriate) with a multidisciplinary approach, in order to taken into account statistical, methodological and clinical aspects of this issue.

Missing data due to the premature discontinuation from the study or treatment are unlikely.

Appropriate measures will be undertaken in order to avoid missing data, including regular double check of completeness of data forms and review of the video recordings.

Missing data will be described in the study report.

## 6.5 Interim Analyses and Data Monitoring

A monitoring board will review all deaths and adverse effects, as described in the trial protocol.

An interim analysis will be performed on the primary endpoint and the serious adverse events (SAEs) from the first 100 infants enrolled. The interim analysis will be performed by the statistician, blinded for the treatment allocation, who will report to the principal investigator. The principal investigator will discuss the results of the interim analysis with the monitoring board and the trial will be ended in case of harm. Criteria for stopping for harm include: a statistically significant difference ( $p < 0.001$  according to Haybittle-Peto boundary or  $p < 0.0294$  according to Pocock boundary) (14) in the primary outcome between the treatment groups; a reasonable suspected causal relationship between the intervention and SAEs.

Stopping for futility and/or interim analysis for sample size adjustment are not planned.

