### **Statistical analysis**

Analysis will be performed according to the “intention to treat” approach. In case of deviations from the protocol regarding the contamination between arms, a per-protocol analysis will be also performed and the conclusion will be drawn according to the results of both analyses. Continuous

data will be expressed as mean and standard deviation, or median and interquartile range. Outcome measures will be compared between the two arms using Chi-square test, Fisher's test, Student *t* test or Mann-Whitney test as appropriate (unadjusted analysis). Regression models (adjusted analysis) will be estimated to evaluate the effect of drying on the outcome measures, adjusting for participating centers and potential confounders (i.e. clinically relevant variables or unbalanced characteristics at baseline). Effect sizes will be reported as risk ratio or mean difference with 95% confidence intervals. A sub-analysis according to gestational age ( $23^{+0}$ - $27^{+6}$  and  $28^{+0}$ - $31^{+6}$  weeks) will be performed with exploratory purpose. A p-value less than 0.05 will be considered statistically significant. Statistical analysis will be performed using R 4.1 software (R Foundation for Statistical Computing, Vienna, Austria) (19).

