**Data Safety and Monitoring Board**

Safety measures will include incidence, severity and causality of reported SAEs, represented by changes in occurrence of the expected common neonatal complications and the development of unexpected SAEs. SAE will be defined as unexpected death, severe hyperthermia (temperature  $>39^{\circ}\text{C}$ ) and hypothermia (temperature  $<35^{\circ}\text{C}$ ). All SAEs will be followed until complete resolution or until the clinician responsible for the care of the recruited patient considers the event to be chronic or the infant to be stable.

A monitoring board including an independent assessor (not involved in the study) from the Azienda Ospedale Università di Padova and assessors from each participating hospital will review all the deaths and adverse effects. If there is a reasonable suspected causal relationship with the intervention, SAEs will be reported to the Ethics Committee to guarantee the safety of the participants.

An interim analysis will be performed on the primary endpoint and SAEs from the first 100 infants enrolled. The interim analysis will be performed by the statistician, blinded for the treatment allocation, who will report to the principal investigator. The principal investigator will discuss the results of the interim analysis with the monitoring board and the trial will be ended in case of harm. Criteria for stopping for harm include: a statistically significant difference in the primary outcome between the treatment groups; a reasonable suspected causal relationship between the intervention and SAEs.

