## 5 Sample Size

Based on literature data (11), we hypothesize that the proportion of neonates in the normal thermal range at NICU admission may increase from 40% in the control arm to 55% in the intervention arm. With a power of 80% and an error I type of 0.05, the minimum sample size is estimated in 346 neonates (173 per arm). As the design is a stratified multicenter individually randomized trial, randomization is balanced and stratified on centers, and we expect no loss of power as a result of randomizing neonates by center (12). Sample size calculations were performed using R 4.1 software (R Foundation for Statistical Computing, Vienna, Austria) (13).

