### 6.2 Approach for main analysis

Data analysis will be performed using the statistical software packages R. All tests will be two-sided and a p-value less than 0.05 will be considered statistically significant. Statistical analysis will include an unadjusted analysis followed by an adjusted analysis.

Analysis will be performed according to the "intention to treat" (ITT) approach. In case of deviations from the protocol regarding the contamination between arms, a per-protocol analysis will be also performed, and the conclusion will be drawn according to the results of both analyses.

Additional sub-group analyses will be considered with exploratory purpose.

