## 8 Analysis of primary outcome measure

The primary outcome measure is the proportion of neonates in the normal thermal range (temperature 36.5-37.5°C) at NICU admission. It will be summarized as frequency with percentage for each arm. In the unadjusted analysis, it will be compared between the two arms using Chi Square test or Fisher's test. The adjusted analysis will involve a generalized mixed-effect regression model including the trial arms (fixed effect), the participating center (random effect) and unbalanced participant characteristics at baseline (fixed effects). Relative risk with 95% confidence intervals for treatment vs. control arms will be calculated in both unadjusted and adjusted analyses, with a confidence interval higher than 1 indicating superiority of the intervention over the control.

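### The SAP names two interim boundaries (p<0.001 or p<0.0294) without choosing one or giving a direction, and the final test stays at 0.05; the Pocock value does not fit this design

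*Combined protocol and SAP*

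**What the plan says.** SAP 6.5 (Interim Analyses and Data Monitoring) plans one interim analysis of the primary endpoint and the SAEs, on the first 100 infants enrolled. Among the criteria for stopping for harm it lists a significant difference at p<0.001 "according to Haybittle-Peto boundary or" at p<0.0294 "according to Pocock boundary) (14) in the primary outcome between the treatment groups". It gives no rule for choosing between the two values and no direction for the difference.

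The protocol's section on the Data Safety and Monitoring Board describes the same look but gives no threshold. Its criterion is "a statistically significant difference in the primary outcome between the treatment groups". The protocol's Statistical analysis section has one general level: "A p-value less than 0.05 will be considered statistically significant". SAP section 13 states that the SAP changes nothing in the protocol's statistical approach.

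The final level is not adjusted for the look. SAP 6.2 says "All tests will be two-sided and a p-value less than 0.05 will be considered statistically significant", and SAP 8 reads superiority from a 95% interval for the relative risk, "with a confidence interval higher than 1 indicating superiority of the intervention over the control". SAP 5 gives the design: "With a power of 80% and an error I type of 0.05, the minimum sample size is estimated in 346 neonates (173 per arm"), for a proportion that "may increase from 40% in the control arm to 55% in the intervention arm".

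**The concern.** A stopping rule has to give one decision for each interim result. Here two thresholds differ by a factor of about 29 (0.0294/0.001), and the text does not say which one governs. The interim result goes to the principal investigator, who then discusses it with the monitoring board. If the boundary is not fixed beforehand, the choice could be made with the p-value already known, and the decision would be open to challenge whichever way it went.

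The two boundaries also carry different obligations at the end of the trial. A Haybittle-Peto look is so strict that the final test can stay almost at its nominal level. Pocock's 0.0294 is the constant for two equally spaced looks with the same level used at both. This plan looks at 29% of the sample and tests at 0.05 at the end.

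Finally, a rule labelled as stopping for harm is written as any difference in the primary outcome. A strong early benefit of drying would meet the written criterion. What is at stake is the stated 5% error and the credibility of an early stop.

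**Working it through.** **Inputs.** Rates of 40% and 55%, two-sided alpha 0.05, 80% power, 346 infants (SAP 5). 1:1 allocation (SAP 4.3). Look at 100 infants, boundaries 0.001 and 0.0294 (SAP 6.5). Final level two-sided 0.05 (SAP 6.2). I assume 50 infants per arm at the look.

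**Step 1: reproduce the sample size.** Mean rate 0.475, no continuity correction:

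n per arm = [1.960·√(2·0.475·0.525) + 0.842·√(0.40·0.60 + 0.55·0.45)]² / 0.15² = 172.8, so 173 per arm and 346 in total.

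This matches SAP 5. The calculation contains no allowance for an interim look.

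**Step 2: where the two boundaries disagree.** Take 20/50 normothermic in one arm and 32/50 in the other. The p-value is 0.016 by uncorrected chi-square, 0.028 with continuity correction and 0.027 by Fisher's test. All three lie between 0.001 and 0.0294, so Pocock says stop and Haybittle-Peto says continue. In simulation (2 million trials, uncorrected chi-square) the interim p falls in this zone about 3% of the time with no effect and about 24% of the time under 40% vs 55%.

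**Step 3: overall type I error.** Information fraction 100/346 = 0.289. Under no effect the interim and final Z are bivariate normal with correlation √0.289 = 0.538.

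Overall error = 1 − P(|Z₁| < c₁ and |Z₂| < c₂)

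Critical values: 3.291 for p = 0.001, 2.178 for 0.0294, 1.960 for 0.05.

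| Interim level | Final level | Either direction counts | Only harm stops |
|---|---|---|---|
| 0.001 | 0.05 | 5.05% | 5.03% |
| 0.0294 | 0.05 | 7.2% | 6.1% |

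For the last column the interim region is Z₁ < −c₁ only. The chance of a false claim of benefit is then 2.50% under both boundaries.

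The binomial simulation agrees. The Pocock option gives 7.6% at a common rate of 40% and 7.4% at 47.5%. The 0.001 option gives 5.2% and 4.7%, against 5.2% and 4.6% for the final test alone.

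**Step 4: does 0.0294 fit this design?** Used at both looks with the first at half the information, it gives 5.00%. With the first look at 0.289 it gives 5.4%. To bring the overall error to 5% after a look at 0.0294, the final level would have to be 0.0251. The documents plan neither.

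**Step 5: does 0.001 fit?** The final level for an overall 5.0% is 0.0495. Power at 346 for 40% vs 55%, counting an interim crossing as a rejection, is 79.8% (pooled variance) or 80.7% (unpooled) with a final 0.05. With a final 0.0495 it is 79.7% or 80.6%.

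**The case against.** The strongest reply is that both documents describe stopping for harm only. On a directional reading, stopping early can never produce a claim of benefit, and the false-benefit rate stays at 2.5% under either boundary. That stands, and it is why the 7.2% must carry its condition. It does not close the point: the written criterion has no direction, the two-sided error is still 6.1% with 0.0294, and the two thresholds still conflict.

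A second reply is that *or* in a list of criteria means that either suffices. The rule is then determinate: p<0.0294. That is a fair literal reading, but it makes the Haybittle-Peto value redundant and selects the boundary that does not fit the final level. It is also true that stopping passes through discussion with the board and is not automatic.

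A reader might infer more than the documents support:

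- **That the 5% error fails whichever boundary is used.** With 0.001 then 0.05 it is 5.05%, which has no practical weight.
- **That the true error is 9.0%.** This takes the protocol's phrase to mean p<0.05 at the look. The general level makes that reading possible, but the SAP supplies specific interim thresholds, so it is not the operative plan.
- **That the 80% power is lost.** This would need a reduced final level, such as 0.0294, and neither document plans one.
- **That an early stop would yield a superiority claim.** SAP 6.1 says only that the final analysis follows the end of enrolment or a stop.
- **That the boundaries translate into fixed event counts.** Against 20/50, a result of 10/50 gives p=0.029 uncorrected but 0.049 by Fisher's test. A result of 5/50 gives 0.0005 uncorrected but 0.0012 with continuity correction. SAP 8 allows chi-square or Fisher's test without saying which applies.

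**Conclusion.** The point holds in this form: SAP 6.5 leaves the interim boundary and its direction open, the protocol gives no boundary, and one of the two listed values does not match the final test. Under the Pocock value, which is also the literal either-suffices reading, the overall two-sided error is about 7.2% if any crossing counts and 6.1% if only harm stops, against the stated 5%. Under Haybittle-Peto the plan is sound as it stands. The sample size of 346 is correct for its stated inputs.

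These figures rest on a look at exactly 100 of 346 infants with complete primary outcomes, equal arms at the look, independent outcomes and the normal approximation. The point should be settled before the 100-infant look, because a boundary chosen after the interim p-value is known cannot be defended.

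**What to change.** In SAP 6.5, state four things: one boundary, the direction in which it applies, the test that gives the interim p-value (chi-square with or without correction, or Fisher's), and the matching final level. Put the same rule in the protocol's Data Safety and Monitoring Board section.

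Of the two listed boundaries, Haybittle-Peto at two-sided p<0.001 with the final test at 0.05 keeps the stated alpha (5.05%), about 80% power and 346 infants. A final level of 0.0495 gives 5.0%. Delete the Pocock alternative. Keeping it would need a final level of about 0.0251 at this timing if crossings in either direction count, and power at 346 would then be about 74%.

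If the rule is directional, also say who identifies the arms, since the interim statistician is blinded to allocation.

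The cost is a sentence or two in each document, with no change to sample size or data collection. The one downside is that stopping early on the primary outcome would need stronger evidence than under Pocock. The separate SAE criterion is unaffected.

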## 7 Summary of Study Data

Data will be summarized as mean with standard deviation or median and interquartile range (continuous data), or frequency with percentage (categorical data). Number of non-missing data, contaminations between arms and lost to follow-up will be reported. Summary of data will be presented in tables.

## 8 Analysis of primary outcome measure

The primary outcome measure is the proportion of neonates in the normal thermal range (temperature 36.5-37.5°C) at NICU admission. It will be summarized as frequency with percentage for each arm. In the unadjusted analysis, it will be compared between the two arms using Chi Square test or Fisher's test. The adjusted analysis will involve a generalized mixed-effect regression model including the trial arms (fixed effect), the participating center (random effect) and unbalanced participant characteristics at baseline (fixed effects). Relative risk with 95% confidence intervals for treatment vs. control arms will be calculated in both unadjusted and adjusted analyses, with a confidence interval higher than 1 indicating superiority of the intervention over the control.

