### 4.3 Randomization and Blinding

Participants will be randomly allocated to intervention or control arms in a 1:1 ratio according to a computer-generated, randomized sequence for each participating hospital. Infants of multiple pregnancies will be randomized as individuals. Randomization (with blocks of size 4-6) will be stratified by center. The randomized allocation will be concealed in double-enclosed, opaque, sealed, and sequentially numbered envelopes. In the delivery room/operating room, the next sequential randomization envelope will be opened only when the neonate will be considered eligible by the attending team, and the assigned procedure will be performed. Contamination between arms will not be allowed. Due to the characteristics of the intervention, neither caregivers nor outcome assessors will be masked to treatment allocation. However, the statistician who will perform data analysis will be blind for treatment allocation.

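### The primary outcome is tested without the centre stratification, by one of two unranked tests, and no analysis is named as decisive; a centre-stratified test costs nothing and fixes this

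*Combined protocol and SAP*

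**What the plan says.** On the primary outcome, SAP Section 8 states for the unadjusted analysis that "it will be compared between the two arms using Chi Square test", and then offers Fisher's test as the alternative. It gives no rule for choosing and does not mention a continuity correction. The protocol's Statistical analysis section lists the same tests, to be used as appropriate.

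SAP Section 8 also plans an adjusted generalized mixed model, with centre as a random effect and any baseline characteristics found to be unbalanced as fixed effects. A relative risk with 95% confidence interval is reported from both analyses, and an interval above 1 is read as superiority.

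SAP Section 6.2 sets the threshold: "All tests will be two-sided and a p-value less than 0.05 will be considered statistically significant". It plans the unadjusted result first and the adjusted one second, and ranks neither.

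On design, SAP Section 4.3 states: "Randomization (with blocks of size 4-6) will be stratified by center". SAP Section 5 assumes that the proportion "may increase from 40% in the control arm to 55% in the intervention arm" and, "With a power of 80% and an error I type of 0.05", arrives at 346 infants, 173 in each arm. It does not name the test behind that figure.

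**The concern.** Three things are left loose in the one analysis on which the trial will be judged.

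- **Stratification.** The trial randomises within centre, but neither unadjusted test uses centre. If centres differ in how often infants arrive in the normal range, such a test overstates the variance of the treatment comparison. It is then conservative and gives up power.
- **Choice of test.** The two named tests do not have the same power at this size. On a borderline result one can be significant and the other not.
- **Decisive analysis.** An unadjusted and an adjusted relative risk will both be reported, and the SAP does not say which one settles the question if they disagree.

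At stake are a few points of power and a clear rule for declaring success. Type I error is not materially inflated by any of these choices.

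**Working it through.** **Inputs.** 40% against 55%, power 80%, alpha 0.05 and 173 per arm (SAP Section 5); two-sided tests (SAP Section 6.2); 1:1 allocation stratified by centre (SAP Section 4.3); 21 centres (SAP Section 4.1). The documents give no between-centre variation, so that is assumed below and shown as a range.

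**1. The plan's own figure.** With pooled variance and no continuity correction:

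n = [1.960 × √(2 × 0.475 × 0.525) + 0.842 × √(0.40 × 0.60 + 0.55 × 0.45)]² / 0.15² = (1.384 + 0.588)² / 0.0225 = 172.8

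This rounds up to 173 per arm, 346 in total. The stated figure is reproduced, and it belongs to an uncorrected chi-square.

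**2. Exact power of each possible test at 173 per arm**, by summing both binomial distributions over all tables:

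| Test | Power, 40% vs 55% | Type I error, 40% in both arms | Type I error, 47.5% in both arms |
|---|---|---|---|
| Chi-square, uncorrected | 79.2% | 5.2% | 4.7% |
| Chi-square, continuity-corrected | 76.0% | 4.0% | 3.6% |
| Fisher | 76.0% | 4.0% | 3.6% |

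The continuity-corrected sample size is (172.8/4) × [1 + √(1 + 4/(172.8 × 0.15))]² = 43.2 × (1 + 1.0744)² = 185.9, or 186 per arm. By exact calculation, 184 per arm already gives Fisher's test 80.4%.

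**3. Would small counts call for Fisher's test?** The expected cells are 173 × 0.475 = 82 and 173 × 0.525 = 91. They would not.

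**4. Can the choice change the result?** Take 69/173 against 88/173. The uncorrected chi-square gives p = 0.040; Fisher's test and the corrected chi-square give p = 0.052. The relative risk is (88/173)/(69/173) = 1.28, with a lower 95% limit of about 1.01 by the log method (an assumption, since the SAP does not name the interval method). At the planned effect, the uncorrected test is significant and the corrected one is not in 3.2% of trials.

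**5. Using centre.** The Cochran-Mantel-Haenszel statistic is z = (A − E)/√V. A is the number of infants in the normal range in the drying arm, E = Σ n₁m/N, and V = Σ n₁n₀m(N − m)/[N²(N − 1)], summed over centres. Within a centre, n₁ and n₀ are the arm sizes, N their sum, and m the number in the normal range.

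The simulation used 20,000 trials, with 16 centres of 8 per arm and 5 of 9 per arm (16 × 8 + 5 × 9 = 173) and overall rates held at 40% and 55%. Centre effects were normal on the logit scale. For scale, around a rate of 40% (logit −0.405), one SD either way spans about 29% to 52% at SD 0.5 and 20% to 64% at SD 1.0.

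| Assumed centre SD (logit) | 0 | 0.5 | 1.0 |
|---|---|---|---|
| Power: chi-square, unstratified, uncorrected | 79% | 80% | 82% |
| Power: Fisher or corrected chi-square | 76% | 77% | 78% |
| Power: Cochran-Mantel-Haenszel, uncorrected | 80% | 82% | 87% |
| Type I error: chi-square, unstratified, uncorrected | 5.1% | 4.6% | 3.1% |
| Type I error: Cochran-Mantel-Haenszel, uncorrected | 5.0% | 5.0% | 4.8% |

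The middle power row comes from the corrected chi-square, whose exact power equals Fisher's in step 2. Repeat runs agree within about one percentage point.

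**The case against.** The best defence is that the natural reading of the plan is consistent. Chi-square is named first. The protocol applies the tests as appropriate, and SAP Section 13 says the protocol's statistical approach is unchanged. With expected cells above 80 there is no ordinary reason to turn to Fisher's test, and the uncorrected chi-square gives exactly the stated 173. The relative-risk interval in SAP Section 8, if computed by the log method, also has 79.2% power. All of this stands.

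Two stronger conclusions are therefore not supported, though a reader might draw them.

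- **That the trial has only 76% power.** That figure depends on a choice the plan permits but does not make. No section mentions a continuity correction. It could still come in unnoticed, because R's standard chi-square function corrects a 2×2 table unless told not to, but that is a software default and not the plan.
- **That the plan ignores centre.** This is true only of the unadjusted test. The adjusted model in the same section of the SAP includes centre, and the protocol also adjusts for it.

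It can also be said that a stratified test beside a centre-adjusted mixed model is redundant. That would hold if the mixed model were named as decisive and fixed in advance. It is neither: no analysis is ranked, and its fixed effects depend on which baseline characteristics turn out unbalanced.

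**Conclusion.** The point holds as a minor one, a free improvement rather than an error. The sample size is right and the plan's most natural reading delivers the stated power. What is missing is one primary test that respects the stratified randomisation and is named as decisive.

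Moving from the unstratified uncorrected chi-square to the centre-stratified test costs nothing if centres do not differ (about 80% against 79%). It gains about 2 points of power at a centre SD of 0.5 and about 5 at 1.0, and holds type I error near 5% where the unstratified test drifts down to about 3%. Closing off Fisher's test and the continuity correction avoids a possible loss of about 3 points (79.2 − 76.0 = 3.2).

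The exact figures rest only on the SAP's inputs. The gains from stratifying rest on the assumed centre SDs, near-equal centre sizes and exact balance within centre.

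**What to change.** In SAP Section 8, replace the choice of chi-square or Fisher's test for the primary outcome with wording such as:

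> The primary outcome will be compared between arms by a two-sided Cochran-Mantel-Haenszel test stratified by centre, without continuity correction. The Mantel-Haenszel relative risk stratified by centre will be reported with its 95% confidence interval. This is the confirmatory analysis; the unadjusted and mixed-model estimates are supportive.

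Keep Fisher's test for sparse secondary outcomes and serious adverse events (SAP Sections 9 and 10). Align SAP Section 6.2 and the protocol's Statistical analysis section, and record the change in SAP Section 13. If Fisher's test were kept as the decisive test instead, 80% power would need about 184 to 186 per arm (368 to 372 in total).

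The cost is a few lines of text, with no added infants and no new data. The change should be dated before outcome data by arm are seen.

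### SAP 8 does not say whether the unadjusted or the adjusted analysis decides the primary outcome, and it picks covariates by observed baseline imbalance instead of fixing prognostic ones in advance

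*Combined protocol and SAP*

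**What the plan says.** SAP 6.2, which sets out the approach for the main analysis, states: "Statistical analysis will include an unadjusted analysis followed by an adjusted analysis". SAP 8 then says: "Relative risk with 95% confidence intervals for treatment vs. control arms will be calculated in both unadjusted and adjusted analyses". Superiority is read from an interval lying above 1, with no distinction between the two analyses. The unadjusted comparison is a chi-square or Fisher test. The adjusted one is a generalised mixed model with arm as a fixed effect, centre as a random effect, and "unbalanced participant characteristics at baseline (fixed effects". SAP 9 repeats this model for the binary secondary outcomes and uses a linear version for temperature at 1 hour.

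The protocol's Statistical analysis section has a wider covariate rule: "adjusting for participating centers and potential confounders (i.e. clinically relevant variables or unbalanced characteristics at baseline". SAP 13 says that the SAP changes nothing in the protocol's statistical approach.

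Gestational age is collected (SAP 4.4) but is not a randomisation stratum, because SAP 4.3 stratifies by centre only. Its one named analytic role is in the exploratory subgroups (SAP 6.3 and the exploratory analyses section). SAP 6.2 also adds a per-protocol analysis if arms are contaminated, and then rests the conclusion on that analysis and the ITT analysis together.

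**The concern.** Two analyses share one decision rule with no order between them, so the plan does not define the trial's result when they disagree. The interim comparison in SAP 6.5 is equally silent on which analysis is meant.

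The adjusted model is also not fixed before the data are seen. No candidate variables, imbalance measure or threshold are given, so two careful statisticians could fit different models to the same data. Under randomisation, baseline imbalance is chance. Adjustment is worthwhile when a covariate predicts the outcome, whether or not the arms happen to differ on it. Under SAP 8, gestational age enters only if it happens to look unbalanced. The protocol's other route to it, clinical relevance, is missing from the SAP.

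At stake are an unambiguous primary result and some precision that could be had at no cost in data.

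**Working it through.** **1. The plan's own figure.** Inputs from SAP 5: an increase "from 40% in the control arm to 55% in the intervention arm", and "With a power of 80% and an error I type of 0.05". SAP 6.2 gives the sidedness: "All tests will be two-sided and a p-value less than 0.05 will be considered statistically significant". With pooled variance under the null and no continuity correction:

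n per arm = [1.960 × √(2 × 0.475 × 0.525) + 0.8416 × √(0.40 × 0.60 + 0.55 × 0.45)]² / 0.15²

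= [1.960 × 0.7062 + 0.8416 × 0.6982]² / 0.0225 = (1.384 + 0.588)² / 0.0225 = 172.8, rounded up to 173.

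The total is 346, as stated, and power at 173 per arm is 80.05%. The sample size therefore rests on the unadjusted comparison and owes nothing to covariates.

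**2. The covariate rule without centre effects.** Simulation with 173 per arm and 6,000 trials per scenario (Monte Carlo error about 0.5 point for power). Assumptions: gestational age as a standard normal covariate with the odds ratio shown, five candidate covariates, and imbalance defined as p < 0.05. The SAP gives none of these. All entries are percentages.

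| Odds ratio per SD | Power, unadjusted | Power, imbalance rule | Power, gestational age fixed in advance | Unadjusted and imbalance verdicts disagree (40% vs 55%) | Type I error, unadjusted or imbalance-adjusted | Type I error, unadjusted or gestational-age-adjusted |
|---|---|---|---|---|---|---|
| 1.0 | 80.3 | 80.3 | 80.8 | 0.7 | 4.9 | 4.9 |
| 1.5 | 79.1 | 79.5 | 81.4 | 1.6 | 5.1 | 5.6 |
| 2.0 | 80.2 | 80.7 | 84.5 | 1.9 | 4.9 | 6.0 |
| 2.5 | 78.9 | 79.9 | 86.1 | 2.1 | 5.3 | 6.7 |
| 3.0 | 78.8 | 79.6 | 88.2 | 2.7 | 5.5 | 7.2 |

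The imbalance rule recovers almost none of the available gain. With a p < 0.05 criterion and true randomisation, any one covariate enters the model in only about 1 trial in 20.

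**3. With centre, as the SAP plans it.** Simulation with random centre effects (assumed centre SD 0.5 to 0.7 on the logit scale, gestational age odds ratio 1.5 to 2.2 per SD, 1,500 trials per scenario, error about 1 point):

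- unadjusted: about 80%
- the SAP's imbalance-adjusted model with centre: 81% to 82%
- centre plus gestational age fixed in advance: 82% to 85%
- unadjusted and imbalance-adjusted verdicts disagree: 2% to 3% of trials
- type I error if either of those two may win: near 5%

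The gain over the SAP's own adjusted model runs from 82 − 81 = 1 point to 85 − 81 = 4 points.

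**4. Protocol against SAP.** The protocol admits covariates that are clinically relevant or unbalanced. SAP 8 and SAP 9 admit only unbalanced ones. SAP 13 declares no change. These three statements do not fit together.

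**The case against.** The best defence is that the intention can be guessed. The sample size comes from the unadjusted test, that test is listed first, and the statistician is blinded. The numerical harm is small as well. This stands in part: disagreement is rare and there is no material type I inflation between the two planned analyses. But order of listing is not a hierarchy. Blinding hides which arm is which, not the two p-values or the imbalances. One can also say that the SAP merely took one of two options in the protocol. If so, it should say so instead of declaring no change.

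A reader might infer four stronger points that the documents do not support:

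- **That planned power is wasted.** It is not. The 346 rests on the unadjusted test, which keeps about 80%.
- **That SAP 5's expectation of no power loss from stratifying by centre holds only if the deciding analysis adjusts for centre.** For the stated 80% this fails: the unadjusted test under centre-stratified randomisation stays at about 80% in simulation. Adjustment adds power, and omitting it does not take away what was planned.
- **That the gain is larger, from setting the chi-square test against a model with centre and gestational age.** That credits the change with the centre term already in SAP 8. If centre is fitted as fixed effects, the logistic model beats the chi-square test by about 2 points even when neither centre nor gestational age matters.
- **That sibling clustering is a defect.** SAP 4.3 says "Infants of multiple pregnancies will be randomized as individuals", and centre is the only random effect. Consecutive envelopes fall in opposite arms with probability about 0.60, so the design effect is 1 − ICC × fraction of multiples × (0.60 − 0.40). With an assumed ICC of 0.3 to 0.7 and 25% to 35% multiples, it runs from 1 − 0.015 = 0.985 to 1 − 0.049 = 0.951. Ignoring siblings is slightly conservative.

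**Conclusion.** The point holds as a gap in pre-specification with a modest numerical effect. The text leaves the deciding analysis open and lets observed imbalance choose the covariates, and the SAP's covariate rule is narrower than the protocol's while SAP 13 denies any change.

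The forgone gain is about 1 to 4 points if gestational age has an odds ratio of 1.5 to 2.2 per SD, and nil if it is not prognostic. The documents do not quantify that association. The outcome is a two-sided temperature band, so hypothermia and hyperthermia both count as failures and the association could be weaker than expected. The disagreement rate depends on the assumed imbalance criterion and centre spread.

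The order of repair matters. Adding gestational age without naming one primary analysis would make things worse: a claim on either the unadjusted or the gestational-age-adjusted test has a type I error of up to 7.2% at an odds ratio of 3.0.

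**What to change.** - **SAP 8:** name one primary analysis in the ITT population, a logistic mixed model with arm, centre (random effect, as already planned) and gestational age, with the form of the gestational age term stated. Give one method for the relative risk, for example marginal standardisation from that model. Say that the superiority rule applies to this estimate alone.
- **SAP 8 and 9:** delete the imbalance-based covariates. Make the unadjusted chi-square comparison a sensitivity analysis. Use the same covariates for secondary outcomes where event counts allow.
- **SAP 6.2:** state that the ITT result decides and that the per-protocol analysis is supportive. Otherwise a second route to two verdicts remains.
- **SAP 13 and the protocol's Statistical analysis section:** reconcile the covariate rules, and record the change.

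The cost is wording, settled before unblinding. Gestational age and centre are already recorded, and the sample size stays at 346. The one drawback is that the primary relative risk becomes model-based instead of a raw 2×2 ratio. The sensitivity analysis will still show the raw ratio.
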